**Figure 2 f2:**
[figure not shown]
Overview of study procedures (Created with BioRender.com).

We have chosen these time points to afford serial profiling while minimising burden and coinciding with routine pregnancy care appointments.

### Sample collection, processing, storage and data generation

Specifically, blood will be collected for transcriptomic (RNASeq) as well as epigenetic (methylation) analysis and plasma harvested for proteomics (via Somalogic Inc.) and metabolomics (via Metabolon Inc.). Cell composition of this blood sample will also be assessed by flow cytometric analysis capturing most innate and adaptive immune subsets, from neutrophils, dendritic cells (DCs) and their subsets, to NK cells, monocytes, as well as most T cell subsets and B cell subsets. The Paxgene tube will be used for transcriptomics. As little as 55 microlitres of blood is required for proteomics and metabolomics, so 5mL per timepoint is sufficient for the proposed testing. Given the longitudinal nature of our study set up, samples will be batch randomized to reduce artifact, as well as corrected using ComBat batch to normalise across multiple analytical runs. Following distributional normalisation, we will apply the full power of longitudinal samples from the same participants, i.e., features will be normalised as change over time within each woman, using the WithinVariation function implemented in the R *mixOmics* package. With this, absolute values will be represented as relative change over time - i.e. biological trajectories. We will analyse multiomic signatures across women to define the immune trajectory of pregnancy. We will then contrast omic signatures across clinical groups (healthy term vs. PTB).

Assessment of the newborn infants’ response to maternal immunisation will focus on the nasal mucosa of the infants born to mothers enrolled in our study. Samples will be obtained on day of life 1 and at 6 weeks of age via a standardised, non-invasive and painless sampling procedure (Nasosorption), well-tolerated by newborn infants (and their parents) (37). These time points were chosen to coincide with infant health checks to reduce additional burden to parents. The neonatal nasal lining fluid absorption devices will be used to extract total proteins contrasting the infants’ developmental trajectory as a function of maternal immunisation status. The method of isolation of total proteins from the nasal lining fluids starts by thawing the devices on ice to preserve the integrity of the cells. Then, 300 ul of elution buffer (PBS (pH7.4) containing 0.05% (v/v) Tween20) is added. The synthetic absorptive matrix (SAM) is then removed from the nasosorption device using forceps by tearing it from the handle using sterile forceps. The SAM is then placed into a spinX column using a new pair of sterile forceps. After a centrifugation of the column and SAM at speed centrifugation(16,000 g) for 30 minutes at 4C, 260 ul of equate is reconstituted into a sterile tube and total proteins are quantified using Pierce BCA protein assay kit The protein identification and quantities will be assessed using Somascan, an untargeted Proteomics platform (Somalogic) capable of detecting more than 7000 proteins in less than 200ul of eluate (200ug/ml). In the testing assays performed by the study team, enough proteins were extracted from infant nasal lining devices and only a portion was used for proteomics analysis. The rest of the samples can be stored and used for targeted protein detection panels if interesting signals are detected from the initial untargeted analysis.

Our group and others have proven that when using this integrated multi-omic approach a sample size of 20 per group will suffice to identify robust (80% power) biological signatures related to pregnancy outcome with a two-sided significance criterion (alpha) of < 0.05. With this in mind, a sample size of 400 participants was chosen, assuming a background rate of PTB of 8%, it was estimated 32 women would delivery prematurely providing >20 per group.

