Our group has also recently shown that one’s “immune baseline” can determine the outcomes of vaccination or infection (29, 30), and that for the immune trajectory of the newborn this ‘baseline’ is influenced by maternal immunity (31, 32). We have also shown that the ‘baseline’ in early life is not a stable steady state (as it is in adults), but a dynamic yet highly predictable (and predictive) trajectory (28). This suggests that impacting the mother’s immune trajectory in pregnancy through maternal immunisation may impact the immune trajectory of the infant. The concept of maternal immunity impacting immune ontogeny of her infant is already widely accepted for maternal antibodies influencing the infant’s antibody response to vaccination (33). But there is growing evidence that this mother-infant interaction goes far beyond adaptive immunity: i) maternal quadrivalent influenza vaccine (QIV) reduces acute airway infections in the infant beyond influenza (34) which may relate to vaccine-induced cytokine responses in the nasal mucosa of her infant (35); ii) maternal diphtheria, tetanus and acellular pertussis (dTpa) immunisation during pregnancy reduces the risk for acute airway infections beyond Bordetella pertussis in infants, which may relate to vaccine-induced cytokine transfer across the placenta (36). The theoretical underpinnings of our rationale for Aim 3 are thus supported by existing evidence. What is lacking is evaluation of the maternal-infant immune dyad in the context of maternal immunisation using the unbiased, systematic approach of systems biology proposed here. Our findings promise not only to unveil the mechanisms related to maternal immunisation but to identify pathways to target to improve the developmental trajectory and well-being of all children in general.

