**Figure 1 f1:**
[figure not shown]
Study Design (Created with BioRender.com).

Clinical data will be collected at baseline including established risk factors for PTB as well as past vaccination history. Pregnancy outcomes will be collected at birth. Venous blood (5mL) will be collected at each timepoint: 10-14 weeks, 20-22 weeks, 26-28 weeks, 34-36 weeks, and at birth (**Figure 2**).

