#### Analysis plan

##### Aim 1

We will compare the immune trajectory of all women with a preterm birth (estimated to be 8% of our total sample size) with a matched control group of women who deliver at term. We will not be performing multiomics on all participants recruited. To assess the immune trajectory in relation to pregnancy outcome longitudinally over time we will identify features both in the univariate and multivariate space. For univariate analysis, differentially expressed (DE) genes, proteins, or metabolites will be identified using DESeq2 v1.26. Correction for multiple comparisons will be done to control for false discoveries, filtering results based on a highly conservative p-value for significance (<0.001). Sparse Partial Least Squares - Discriminant Analysis (sPLS-DA) will be used to identify discriminatory features that co-vary with each other. Given the user-defined sparsity feature of sPLS-DA, and with the readout being classification accuracy, no p-value adjustment is necessary for this method. To assess the data in their biological context, i.e. integrated multi-omics, we will use two complementary integration strategies. *NetworkAnalyst* is based on known protein-protein interaction (PPI) networks and *DIABLO*, part of the *mixOmics* framework, a data-driven multi-omic integration approach. Given that *DIABLO* selects features that allow maximum class distinction (i.e. accurate classification of pregnancy outcome), this approach will also identify the earliest point during pregnancy that can accurately predict an adverse birth outcome. Finally, time course analyses that generate smoothing splines allow identification of groups of features that follow the same trajectory in a multivariate space. The *DynOmics* toolbox is an extension of the *mixOmics* toolbox used for multi-omic datasets built to identify these dynamic longitudinal changes in biological systems, while integrating multi-omic data.

##### Aim 2

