We will compare the immune trajectory of 20 unvaccinated women with 20 women who received either one of the two vaccines recommended in pregnancy, and 20 vaccinated with both vaccines. Recruitment started prior to the availability of COVID-19 vaccines but continued during the rollout of COVID-19 vaccines. Data on any vaccination during pregnancy is captured and will be taken into account in the analysis. Based on our previous work, we expect ~10 women in our cohort to choose to not be vaccinated at all, and approximately 50 women to be vaccinated with either influenza or pertussis alone. If we are unable to recruit 10 controls who have received no vaccination we intend to use women who are vaccinated late in pregnancy as a control over the time periods they remain “unvaccinated”. We will employ the same blood processing and data analysis pipeline summarised for Aim 1.

##### Aim 3

Samples will be obtained on day of life 1 and 6 weeks of life (day of recommended first follow up) via our highly standardised, non-invasive thus non-painful sampling procedure (Nasosorption), well-tolerated by newborn infants (and their parents) as described. We will process and analyse these 120 samples as described above contrasting the infants’ immune trajectory as a function of maternal immunisation status.

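### Converting every feature to within-woman change before comparing women removes level differences between groups and, if each woman's own mean is subtracted, lets later samples into the early-prediction analysis

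*Protocol article*

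**What the plan says.** The section on sample collection, processing, storage and data generation sets an order of steps. After batch correction and distributional normalisation, "features will be normalised as change over time within each woman, using the WithinVariation function" of the mixOmics package. The stated result is that "absolute values will be represented as relative change over time - i.e. biological trajectories". The group comparison comes afterwards: "We will then contrast omic signatures across clinical groups (healthy term vs. PTB"). No feature or analysis is exempted.

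Under Aim 1, the Analysis plan names DESeq2, sPLS-DA, DIABLO and spline time courses. Of DIABLO it says that "this approach will also identify the earliest point during pregnancy that can accurately predict an adverse birth outcome". For the vaccine groups of Aim 2: "We will employ the same blood processing and data analysis pipeline summarised for Aim 1".

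Blood is taken at "10-14 weeks, 20-22 weeks, 26-28 weeks, 34-36 weeks, and at birth". Women may enrol between 9 and 22 weeks. The Rationale says that a person's immune baseline "can determine the outcomes of vaccination or infection".

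**The concern.** PTB status is a property of the woman, and so is vaccination status when the dose precedes her first sample. A transformation that keeps only change within a woman cannot show a difference that she carries at every visit. A stable PTB signature would be lost, and baseline level could not contribute to either contrast.

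Two further problems arise if change means deviation from the woman's own mean. That mean includes her later samples, so an early value is not known until she has delivered. It also covers fewer and earlier visits when she delivers early, so the outcome itself alters the values being compared. At stake are the term v PTB contrast and the claim to locate the earliest predictive visit, which would then not be computable prospectively.

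**Working it through.** **The plan's own figures.** 400 x 0.08 = 32 preterm births, as stated. The 80% power at 20 per group comes without an effect size. It corresponds to d = (1.96 + 0.84) x sqrt(2/20) = 0.89 (normal) or 0.91 (t-test), so about 0.9 SD is used below.

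**Assumptions (not in the documents).** Total SD is 1, half the variance between and half within women (correlation 0.5). Visits are at 12, 21, 27 and 35 weeks, with term birth at 39.5. The function subtracts the woman's mean over her available samples; subtracting the first sample is the alternative. Groups are compared by t-test.

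**1. Difference present at all visits.** If group B lies d above group A at every visit, a woman's mean also rises by d, and the centred difference is d - d = 0. Subtracting the first sample gives the same result. Simulated power for about 0.9 SD, 20 v 20:

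| Values compared | Power |
|---|---|
| One raw visit | about 80% |
| Woman means | 93-94% |
| After the within-woman step | 5% |

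For an effect of 1 SD that starts between visits 2 and 3, the mean is 3/5 = 0.6 and the centred profile is -0.6, -0.6, +0.4, +0.4, +0.4. The step of 1 survives, but its position moves. Likewise, late-vaccinated women used as controls for their unvaccinated period would carry -2/5 = -0.4 SD at visits 1-3 if a 1 SD effect began at visit 4.

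**2. Later samples in an early value.** Let the groups differ only at birth, by D. The centred first-visit value shifts by -D/5. Its variance is 0.5 x 4/5 = 0.4, so AUC = Phi[(D/5) / sqrt(0.8)].

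| D (SD) | AUC, centred first visit | Raw |
|---|---|---|
| 1 | 0.59 | 0.50 |
| 2 | 0.67 | 0.50 |
| 3 | 0.75 | 0.50 |

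With first-sample subtraction, or centring only on samples up to each visit, the first value is exactly 0 for every woman. The first visit cannot be properly assessed under any of these readings.

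**3. Unequal visit sets.** The mean sampling week at term is (12 + 21 + 27 + 35 + 39.5)/5 = 26.9. For birth at 33 weeks it is (12 + 21 + 27 + 33)/4 = 23.25. A common trend therefore creates a false difference at every shared visit of 26.9 - 23.25 = 3.65 weeks x slope.

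Simulated false positives at the first visit, 20 v 20, no true difference, preterm births uniform over 30-37 weeks (assumed), range over repeated runs:

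| Common trend | p<0.05 | p<0.001 |
|---|---|---|
| 0.5 SD in total | 5-6% | about 0.1% |
| 1 SD in total | 8-9% | about 0.4% |
| 2 SD in total | 16-18% | about 1% |
| 0.1 SD/week (0.1 x 27.5 = 2.75 SD) | 27-30% | about 3% |
| 0.2 SD/week (0.2 x 27.5 = 5.5 SD) | 74-77% | 21-25% |

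Raw first-visit values stay at about 5%. If 75% of preterm births fall at 35-37 weeks (also assumed), the two steep slopes give 11% and 29% at p<0.05, and 0.5% and 1.9% at p<0.001.

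With first-sample subtraction, a missing 34-36 week sample causes no artefact (5-6%). A missing first sample, which enrolment up to 22 weeks allows, then matters more: if one whole group lacked it, false positives at 26-28 weeks would be 8%, 17% and 54% for rises of 0.5, 1 and 2 SD.

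**The case against.** The strongest reply is that change is the declared target. All three aims concern the immune trajectory, and the plan says openly that levels are replaced by change. This stands: losing level is partly intended and is not an error in a trajectory analysis. It does not justify having no analysis of level, nor letting later samples into an early predictor.

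Several stronger readings are tempting but unsupported:

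- **Baseline as decisive for PTB.** The Rationale ties baseline to vaccination and infection outcomes, not to PTB. It also describes the early-life baseline as a changing trajectory, which favours studying change.
- **All vaccine effects vanish.** Only those present at every sample do. Aim 2 concerns doses in pregnancy, many of which may fall between visits.
- **Large artefacts in general.** The documents give no gestational slope and no distribution of preterm timing. For modest trends or mostly late preterm births the artefact is small, and at the planned univariate threshold of 0.001 it is about 1% or less except for steep trends.
- **Aim 3 is certainly affected.** The step is described for each woman. The cross-reference for the infant samples may mean only the nasal-sample workflow.

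The t-tests above are also not the planned methods. DESeq2 is count-based and may be run before the step, and no error rate was computed for sPLS-DA or DIABLO. That limits the precision of the figures but not the algebra. Finally, handling of unequal visits could properly sit in an unseen analysis plan. The point here is not that such detail is absent, but that the stated rule, applied as written, has these consequences.

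**Conclusion.** The concern holds in a limited form. Loss of any difference present at all of a woman's samples is certain under any within-woman change score (about 80% power to 5% at 0.9 SD), so level cannot contribute to the term v PTB or vaccine contrasts.

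The use of later samples at the first visit and the artefact from early delivery both depend on mean subtraction, which the documents do not state. Under first-sample subtraction the first visit carries no information at all, and the artefact moves to women without a first sample. The size of the artefact depends on assumed trends and delivery times and runs from negligible to large. For an exploratory study this is a should-fix.

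**What to change.** Keep the trajectory analysis and reserve WithinVariation for within-woman questions, such as the effect of gestation or before v after a dose. Then:

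- **Between-group contrasts.** Use batch-corrected, transformed, uncentred values in a mixed model per feature, with a random intercept for woman, gestational age at sampling, group, and group x gestational age. Report both level and change.
- **Prediction at visit t.** Fit sPLS-DA and DIABLO per visit on uncentred values, using only samples taken up to t, with cross-validation by woman.
- **Infants.** If the same step is meant for the two nasal samples, analyse the day 1 level and the change to 6 weeks separately. Otherwise only the change remains, and an effect that persists from day 1 disappears.

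The cost is revised wording and some extra analysis; no new samples are needed. The drawback is that between-woman variation returns to the classifiers.

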#### Analysis plan

##### Aim 1

We will compare the immune trajectory of all women with a preterm birth (estimated to be 8% of our total sample size) with a matched control group of women who deliver at term. We will not be performing multiomics on all participants recruited. To assess the immune trajectory in relation to pregnancy outcome longitudinally over time we will identify features both in the univariate and multivariate space. For univariate analysis, differentially expressed (DE) genes, proteins, or metabolites will be identified using DESeq2 v1.26. Correction for multiple comparisons will be done to control for false discoveries, filtering results based on a highly conservative p-value for significance (<0.001). Sparse Partial Least Squares - Discriminant Analysis (sPLS-DA) will be used to identify discriminatory features that co-vary with each other. Given the user-defined sparsity feature of sPLS-DA, and with the readout being classification accuracy, no p-value adjustment is necessary for this method. To assess the data in their biological context, i.e. integrated multi-omics, we will use two complementary integration strategies. *NetworkAnalyst* is based on known protein-protein interaction (PPI) networks and *DIABLO*, part of the *mixOmics* framework, a data-driven multi-omic integration approach. Given that *DIABLO* selects features that allow maximum class distinction (i.e. accurate classification of pregnancy outcome), this approach will also identify the earliest point during pregnancy that can accurately predict an adverse birth outcome. Finally, time course analyses that generate smoothing splines allow identification of groups of features that follow the same trajectory in a multivariate space. The *DynOmics* toolbox is an extension of the *mixOmics* toolbox used for multi-omic datasets built to identify these dynamic longitudinal changes in biological systems, while integrating multi-omic data.

##### Aim 2

We will compare the immune trajectory of 20 unvaccinated women with 20 women who received either one of the two vaccines recommended in pregnancy, and 20 vaccinated with both vaccines. Recruitment started prior to the availability of COVID-19 vaccines but continued during the rollout of COVID-19 vaccines. Data on any vaccination during pregnancy is captured and will be taken into account in the analysis. Based on our previous work, we expect ~10 women in our cohort to choose to not be vaccinated at all, and approximately 50 women to be vaccinated with either influenza or pertussis alone. If we are unable to recruit 10 controls who have received no vaccination we intend to use women who are vaccinated late in pregnancy as a control over the time periods they remain “unvaccinated”. We will employ the same blood processing and data analysis pipeline summarised for Aim 1.

##### Aim 3

Samples will be obtained on day of life 1 and 6 weeks of life (day of recommended first follow up) via our highly standardised, non-invasive thus non-painful sampling procedure (Nasosorption), well-tolerated by newborn infants (and their parents) as described. We will process and analyse these 120 samples as described above contrasting the infants’ immune trajectory as a function of maternal immunisation status.

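### DESeq2, a model for raw integer counts, is named as the univariate test for SomaScan proteins and Metabolon metabolites, which are continuous intensities; a continuous-data model is needed for these layers.

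*Protocol article*

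**What the plan says.** Under Analysis plan, Aim 1, the protocol article fixes one univariate tool, with its version, for three kinds of feature: "differentially expressed (DE) genes, proteins, or metabolites will be identified using DESeq2 v1.26". This sits within an analysis in which "longitudinally over time we will identify features both in the univariate and multivariate space". Results are filtered at p<0.001.

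The section on sample collection, processing, storage and data generation gives the sources of the data. For the transcriptome, "blood will be collected for transcriptomic (RNASeq) as well as epigenetic (methylation) analysis". For the other two layers, "plasma harvested for proteomics (via Somalogic Inc.) and metabolomics (via Metabolon Inc".

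The same section describes the preparation of the data. Samples are "corrected using ComBat batch to normalise across multiple analytical runs"; then, after distributional normalisation, "features will be normalised as change over time within each woman, using the WithinVariation function implemented in the R" mixOmics package, so that "absolute values will be represented as relative change over time". The contrast of term with preterm birth is mentioned after these steps.

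Maternal blood is taken at "10-14 weeks, 20-22 weeks, 26-28 weeks, 34-36 weeks, and at birth" (Recruitment and procedures). Aim 2 reuses the Aim 1 pipeline. Aim 3 has 120 infant nasal samples, taken on day 1 and at 6 weeks, to be analysed as set out earlier; these are SomaScan protein measurements, with more than 7000 proteins detectable.

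**The concern.** DESeq2 is built for sequencing reads. Its size factors, its mean-dispersion trend and its negative binomial likelihood all presuppose raw integer counts. SomaScan reports relative fluorescence and Metabolon reports mass-spectrometry intensity; neither is a count of sampled units, and their variance need not follow Poisson sampling noise plus overdispersion. That is general methods knowledge and is not stated in the article.

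An analyst who follows the sentence literally meets one of two outcomes for proteins and metabolites. Either the software rejects non-integer input, or the values are rounded and the p-values come from an error model with no justification for those data. Aim 3 is the most exposed, because all its data are proteins and no other univariate method is stated for it. A tool that cannot be used as written also has to be replaced during the analysis. With thousands of features and the outcome groups known, that leaves room for selective choice.

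**Working it through.** **Inputs from the article.** One univariate method (DESeq2) for genes, proteins and metabolites; RNA-Seq, SomaLogic and Metabolon as sources; ComBat followed by within-woman change; up to five maternal samples and two infant samples; threshold p<0.001. The plan gives no operating characteristic for the univariate test that could be reproduced. The Aim 3 total is consistent with the Aim 2 groups: (20 + 20 + 20) infants × 2 time points = 120 samples, all protein data.

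**Step 1: data type against model.**

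| Layer | Source | Scale | Suits DESeq2? |
|---|---|---|---|
| Genes | RNA-Seq | counts, if left raw | yes |
| Plasma proteins | SomaLogic | continuous | no |
| Metabolites | Metabolon | continuous | no |
| Infant nasal proteins (Aim 3) | SomaLogic | continuous | no |

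This step needs no assumed parameter and does not depend on how visits are handled.

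**Step 2: what the normalisation does, if its output is the input.** Within-woman centring replaces each value by its deviation from that woman's mean. The deviations sum to zero, so unless all her values are equal at least one is negative. They are generally not integers. In a simulation of 40 women with five visits and negative binomial counts of mean 200, 52.5% of the centred values were negative and 70% were non-integer; for simulated continuous intensities 57.5% were negative. DESeq2 accepts neither. Centring also sets each woman's mean to 0, so the pooled between-group difference is 0 by construction, and only differences in time pattern remain testable.

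**Step 3: repeated samples (conditional).** This applies only if uncentred visits were pooled with no term for the person. With m samples per person and within-person correlation ρ (not in the article; assumed 0.3 to 0.7), the standard error of a between-group contrast is too small by √(1 + (m − 1)ρ). The actual two-sided error at nominal 0.001 is 2 × [1 − Φ(3.2905 / √(1 + (m − 1)ρ))].

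| m | ρ | SE factor | Actual error at nominal 0.001 |
|---|---|---|---|
| 5 | 0.3 | √2.2 = 1.48 | 0.0265 |
| 5 | 0.5 | √3.0 = 1.73 | 0.0575 |
| 5 | 0.7 | √3.8 = 1.95 | 0.0914 |
| 2 | 0.3 | √1.3 = 1.14 | 0.0039 |
| 2 | 0.5 | √1.5 = 1.22 | 0.0072 |
| 2 | 0.7 | √1.7 = 1.30 | 0.0116 |

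A simulated negative binomial Wald test (a simple moment-based version, not DESeq2 itself; 20 women per group, five samples each, correlation about 0.5, 20,000 replicates) gave 0.059 at nominal 0.001, which agrees with the formula. With one sample per woman it gave 0.0026.

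Five is the maximum m. Women recruited after 14 weeks miss the first sample, and those who deliver before 34 weeks miss the 34-36 week one.

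Steps 2 and 3 are alternatives. Centring removes the shared woman-level component that drives Step 3, so the two cannot both describe the same data. Neither measures the mismatch in Step 1.

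**The case against.** It can be said in the plan's favour that the article condenses a fuller plan, and that two stronger charges go beyond its text. Both objections stand.

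First, a reader might infer that DESeq2 is specified for data already corrected by ComBat and centred within women. That is the natural reading, since no raw-count branch is described, but it is not stated. The within-woman function belongs to the mixOmics package, and so could feed only the multivariate methods while DESeq2 receives raw RNA counts.

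Second, a reader might infer that repeated samples will be treated as independent women and that the p<0.001 threshold is therefore inflated. The article does not say that visits are pooled. DESeq2 has no random effects, but it can be run visit by visit, or with woman as a fixed effect for within-woman or group-by-time contrasts. The design formula is detail that an article may leave to the full plan.

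It can be added that this is a mechanistic, observational study and that DESeq2 is one step among several. That is fair: sPLS-DA, DIABLO and the spline time courses are outside this point.

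None of this rescues DESeq2 for proteins and metabolites. There the article does not leave a gap; it names a tool that does not suit the data.

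**Conclusion.** The point holds for the data type. The article assigns a raw-count model to two feature types of the three it names, and through reuse of the pipeline to the Aim 2 plasma proteins and metabolites and all 120 Aim 3 samples. This rests only on the quoted sentence, the named platforms and general knowledge of what DESeq2 accepts. The size of the resulting p-value error cannot be derived from the documents.

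The normalisation conflict is real if the within-woman changes are the DESeq2 input, which the article suggests but does not state. The inflation figures (about 2.7% to 9.1% with five samples, about 0.4% to 1.2% with two, at nominal p<0.001) rest on an assumed correlation of 0.3 to 0.7 and on pooling that the article does not describe. They should be quoted only with those conditions. DESeq2 on raw RNA-Seq counts is sound. The sentence should be corrected before omics results are compared between groups.

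**What to change.** Replace the single sentence with one statement per layer, and say which version of the data enters each test.

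- **RNA-Seq genes:** DESeq2 on raw counts, with batch as a design term and no prior ComBat or within-woman centring. Run it per visit, or with woman as a fixed effect for within-woman or group-by-time contrasts. In the latter model a separate batch term is redundant if all of a woman's samples share a batch, as the Quality control section intends.
- **Plasma proteins and metabolites:** a linear model on log-transformed values (limma or a mixed model), with a woman-level effect whenever time points are analysed together.
- **Aim 3 nasal proteins:** the same linear approach, with an infant-level effect when day 1 and 6 weeks are analysed together.

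The choice of package is secondary; a continuous-data model and a person-level term are what matter. The cost is analysis wording and freely available software. Sample size, visits and assays do not change.

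### Aim 1 reads good class separation in a PTB-versus-matched-control subset as accurate prediction of preterm birth, which that subset alone cannot show for a cohort with 8% PTB

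*Protocol article*

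**What the plan says.** Protocol article, Analysis plan, Aim 1, sets up the comparison thus: "We will compare the immune trajectory of all women with a preterm birth (estimated to be 8% of our total sample size) with a matched" group of term deliveries. It adds: "We will not be performing multiomics on all participants recruited". The analysed set is therefore chosen on outcome: all cases, and a selection of non-cases.

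For sPLS-DA, the same paragraph dispenses with p-value adjustment, partly "with the readout being classification accuracy". For DIABLO, it describes feature selection as aiming at the best separation of the outcome classes, which it equates with classifying pregnancy outcome accurately. From that property it concludes that "this approach will also identify the earliest point during pregnancy that can accurately predict an adverse birth outcome".

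The sample-size paragraph, at the end of the section on sample collection, processing, storage and data generation, gives the cohort figures: "a sample size of 400 participants was chosen, assuming a background rate of PTB of 8" per cent, from which "it was estimated 32 women would delivery prematurely providing >20 per group".

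The article does not bring the prediction statement back to the 8% rate, nor does it limit the statement to the matched set.

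**The concern.** Separating cases from selected controls and predicting the outcome among pregnant women are different questions. The first can be answered in a set where PTB makes up half, a third or a fifth of the women, depending on the matching ratio. The second depends on the true share of PTB, because at 8% even a modest false-positive rate among the many term women outweighs the true positives.

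Cross-validation does not remove the difference. A perfectly validated classification rate in the matched set is still a rate for that mix of cases and controls.

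At stake is one stated conclusion of Aim 1: that a given visit is the earliest at which PTB can be predicted accurately. If it is reported from subset performance alone, readers may take it to mean that most women flagged at that visit would deliver preterm, when the reverse may hold. The abstract expects the results to identify targets for later intervention studies, so the meaning of an early predictive visit matters.

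**Working it through.** **Inputs from the document.** Cohort of 400; PTB rate 8%; all PTB cases and only a matched subset of term women assayed.

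**Inputs not in the document, assumed.** Matching ratio: 1:1, with 1:2 and 1:4 also shown. Sensitivity (Se) and specificity (Sp): a range.

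**The plan's own figure.** 400 × 0.08 = 32 PTB cases, as stated. The remaining 400 − 32 = 368 women deliver at term.

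**Formula.** With PTB share p in the set considered, PPV = Se·p / [Se·p + (1 − Sp)(1 − p)].

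**Worked case, Se = Sp = 0.80.**
- 1:1 subset, p = 0.50: 0.40 / (0.40 + 0.10) = 80%. Accuracy is also 80%.
- Cohort, p = 0.08: 0.064 / (0.064 + 0.184) = 25.8%.
- In counts: true positives 32 × 0.80 = 25.6; false positives 368 × 0.20 = 73.6. About 74% of flagged women deliver at term.

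**Other values, Se = Sp = s.**

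| s | PPV, 1:1 | PPV, 1:2 | PPV, 1:4 | PPV, cohort (8%) |
|---|---|---|---|---|
| 0.70 | 70% | 54% | 37% | 17% |
| 0.80 | 80% | 67% | 50% | 26% |
| 0.90 | 90% | 82% | 69% | 44% |
| 0.92 | 92% | 85% | 74% | 50% |
| 0.95 | 95% | 90% | 83% | 62% |

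For given Se and Sp the cohort PPV does not depend on the matching ratio; only the subset figure moves.

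**When does the cohort PPV reach 50%?** Setting Se × 0.08 = (1 − Sp) × 0.92 gives Sp = 1 − Se × 0.08/0.92. The specificity needed is 93.0% at Se = 0.80 and 94.8% at Se = 0.60. With Se = Sp the solution is 0.92.

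**Unequal Se and Sp.**

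| Se | Sp | Accuracy, 1:1 | Accuracy, cohort | PPV, cohort |
|---|---|---|---|---|
| 0.90 | 0.70 | 80% | 0.08 × 0.90 + 0.92 × 0.70 = 71.6% | 20.7% |
| 0.70 | 0.90 | 80% | 0.08 × 0.70 + 0.92 × 0.90 = 88.4% | 37.8% |
| 0.60 | 0.95 | 77.5% | 0.08 × 0.60 + 0.92 × 0.95 = 92.2% | 51.1% |

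The first two rows have the same accuracy in the 1:1 set but cohort PPVs of 21% and 38%. Subset accuracy alone cannot tell them apart.

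**The case against.** **Purpose.** Aim 1 is about immune trajectories and mechanism. Sampling on outcome is legitimate for finding features and, subject to the matching, for estimating sensitivity and specificity. The article proposes no screening threshold and makes no PPV claim. This stands, and it confines the point to one sentence.

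**Joined text.** Classification accuracy is named as the readout of sPLS-DA, whereas the prediction sentence concerns DIABLO, and no rule for naming a visit is given. That is correct, but the DIABLO sentence rests on accurate classification of the outcome, which is the same criterion in substance.

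**Condensed article.** Metrics, matching ratio and weighting are commonly left to a full protocol or SAP, which are not shown. Their absence is not the complaint. The article prints both a conclusion and the reason for it, and the reason does not support the conclusion.

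**Stronger readings.** A reader might infer three things that the documents do not support.
- *That such a classifier has no predictive value.* At Se = Sp = 0.80, a PPV of 26% is about 3.2 times the 8% base rate (25.8/8), and NPV is 294.4/(294.4 + 6.4) = 98%. Calling every woman term would be 92% accurate but would detect no PTB.
- *That the subset always flatters.* With cases over-represented this holds for PPV, not for accuracy: Se 0.70 and Sp 0.90 give 80% at 1:1 and 88% in the cohort.
- *That a false-positive rate can be attached to declaring a visit predictive.* The protocol states no null hypothesis for accuracy and plans no test of it against chance.

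**Conclusion.** The concern holds, limited to the prediction statement. Class separation in an outcome-selected set shows discrimination from the chosen controls and does not by itself establish accurate prediction at an 8% PTB rate.

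The size depends on assumptions that the document does not supply. With 1:1 matching and Se = Sp = 0.80, PPV falls from 80% in the subset to about 26% in the cohort. With Se = Sp, most flagged women would deliver at term at any value below 0.92. This is not inevitable, since a sufficiently specific classifier takes PPV above 50%.

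The trajectory comparison and feature discovery stand as planned, and the classifier may still be informative.

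**What to change.** In Aim 1, for each visit report cross-validated sensitivity, specificity and AUC. Add PPV and NPV weighted to the observed cohort PTB rate, with intervals, giving each term control the inverse of her sampling fraction (within matching stratum where controls are matched). Base any statement about prediction, including the earliest visit, on these measures. Otherwise, word the result as the earliest visit that discriminates PTB from matched term controls.

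No new assays are needed, because the enrolled cohort is the sampling frame. The predictive figures will look less favourable and be imprecise. At 1:1, about 32 controls would each carry a weight of about 368/32 = 11.5, so one misclassified control adds about 11.5 false positives.

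To illustrate: if 26 of 32 controls were classified correctly, specificity would be 81%, with an exact 95% interval of 64% to 93%. Holding sensitivity at 0.80, PPV would be 0.064/(0.064 + 0.92 × 0.1875) = 27%. The interval limits for specificity give 0.064/(0.064 + 0.92 × 0.364) = 16% and 0.064/(0.064 + 0.92 × 0.072) = 49%. That width belongs in the report.
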